# **The effect of different Russian Current parameters on maximum voluntary isometric contraction of the quadriceps muscle among University of Sharjah students: A study protocol for a randomized controlled trial**

## **Abstract**

**Background:** Neuromuscular electrical stimulation (NMES) is widely used in rehabilitation that stimulates the peripheral nerve to cause visible muscle contraction to strengthen weak muscles. Physiotherapists utilized a variety of electro-motor stimulation modalities to enhance muscle performance, muscle reeducation, decrease muscle spasticity, and postpone atrophy. One of the most well-known neuromuscular electrical stimulations is the Russian current, recommended for boosting muscle strength due to its high tolerance and low pain provocation. As individual NMES parameters have not been clearly evaluated in literature, independent evaluation of individual NMES parameters can provide clinically relevant information on how NMES might be optimized to promote strength muscle training in both healthy and afflicted subjects. Of interest, an example of a parameter that has not received significant attention is the expert mode.

## **Methods**

This is a single-blinded, block-randomization controlled trial in a prospectively controlled laboratory. Sixty-six healthy university students will be recruited from the University of Sharjah, United Arab Emirates (UAE). The volunteers will be divided into three systemically randomized experimental groups. Each group will be admitted to a program of training utilizing one of three expert modes of the Russian current. The electrically elicited quadriceps muscle extensor torque

will be measured in response to modes at the participants' maximum tolerance at three points before the start of training, after three weeks of training, and at the six-week follow-up by the Biodex isokinetic system.

## **Hypothesis**

We hypothesize that electrically induced torque of the quadriceps muscle in healthy persons will be differently affected by various Russian current modes.

## **Impact**

Russian current parameters have previously been researched, including phase duration, pulse duration, duty cycle, carrier frequency, and waveform type. However, there are no studies that have investigated how expert modes affect the quadriceps muscle's maximum voluntary isometric contraction.

## **Trial registration**

The study is officially registered at [www.clinicaltrials.gov](http://www.clinicaltrials.gov) (NCT05303181). Date 21/3/2022, and approved by the Research Ethics Committee, University of Sharjah (REC-22-02-28-S). Date 28/2/2022

## 1.Introduction

Neuromuscular electrical stimulation (NMES) is a type of physical therapy modality that uses electrical pulses to strengthen weakened muscles, which stimulate the peripheral neurons and result in contraction of muscle tissue. The amount of torque generated throughout the stimulation application is used to evaluate strength gains. NMES has been promoted as being more beneficial than exercise alone during the early phases of recovery. It has been well established in the literature that NMES can increase quadriceps femoris muscle strength; patients admitted to NMES training for 4 to 5 weeks at 3 sessions per week, had their quadriceps femoris muscle strength increased by about 14.0% to 48.5%. [1-7]. Multiple factors such as the well-being of the patient, position of the electrodes, frequency and current intensity, waveform, burst frequency, and duration encouraged researchers to investigate the best parameters to enhance muscle performance and minimize the discomforting because of the use of NMES.

Selkowitz et al. observed a 44% increase in quadriceps femoris muscle strength when training at an intensity of 91% of the maximum voluntary isometric contraction (MVIC) force.

On the other hand, according to Lai et al., investigating the effects of NMES training at 25% and 50% of the maximal voluntary isometric contraction, there was a corresponding increase in quadriceps femoris isometric strength of 24.2% and 48.5% [7]. Furthermore, Snyder-Mackler et al. [6] reported that after anterior cruciate ligament restoration, the intensity of NMES training was found to be positively correlated ( $r = 0.756$ ,  $P 0.05$ ) with the recovery of quadriceps femoris muscle strength. These investigations proved that increasing the intensity of the training stimulus (%MVIC) influenced muscle strength following NMES.

Motor unit recruitment during voluntary contraction follows the size principle as described by Henneman, Milner-Brown, and Jabre and Spellman [8]. According to this principle, small motor

units (with type I skeletal muscle fibers) are recruited first, followed by the large motor units (with type II skeletal muscle fibers) as the force demand increases during voluntary contraction [9]. Moreover, the order of recruitment of type II fibers occurs in the following order: first type IIa fibers, and then type IIb fibers. However, it has been suggested that NMES leads to an inversion of the size principle, in which recruiting larger (fast) motor units before the slow. This theory is based on two well-established findings: A larger motor unit's axons have a lower threshold for excitability, and data show increased fatigue in the NMES compared to voluntary activation [10, 11]. Theoretically, voluntary muscle contraction that is enhanced by electrical stimulation should result in a more powerful muscle contraction due to an increase in force production due to additional muscle fiber recruitment in acute application of electrical stimulation and subsequently improve muscle power, strength, and endurance in chronic application [9, 12]. A later study reported that voluntary muscle contraction and electrical stimulation causes different actions in muscle fiber and metabolism [13].

“What are the optimal stimulus parameters for eliciting forceful, yet comfortable, electrically induced muscle contractions?” To answer this question, a lot of research has been done to find which parameters are clinically adopted in producing depth-efficient stimulation of nerve and muscle. Therefore, selecting the best waveforms and time modulations to maximize muscle torque is a critical clinical factor. Laufer et al. [4] assessed which waveforms and current produced the greatest electrically induced torque (EIT) and minimal fatigue in the quadriceps femoris muscles. The study concluded that a sinusoidal waveform of 2500-Hz alternating current that was 50% burst modulated generated more fatigue and smaller EITs [% of maximum voluntary isometric contraction (MVIC)] compared to a biphasic rectangular symmetrical pulsed current. Using a 2500-Hz alternating current, McLoda and Carmack [14] studied the effects of various burst duty

cycles on the EIT (%MVIC) of the quadriceps femoris muscles. They found that the EIT was greatest at a burst duty cycle of 10% and the least at 90%. This implies that a lower duty cycle on time results in a higher EIT.

According to Snyder-Mackler et al. [15], stimulation of the quadriceps femoris muscle group with the 2500-Hz alternating current (P.01) or the symmetrical rectangular pulsed current (P.05) resulted in stronger EITs than stimulation with the 4000-Hz.

Similarly, Ward and Robertson [16] found that the EIT of the wrist extensor muscles decreased linearly as the alternating current carrier frequencies were raised from 1000 to 15000 Hz.

According to the findings of these two previous studies, it might be possible to enhance the amount of EIT and reduce the current amplitude necessary to produce the greatest EIT response by utilizing burst-modulated alternating current with a lower carrier frequency and longer phase length.

Russian currents are medium frequency burst alternating currents with a carrier frequency of 2500 Hz and one of the most well-known neuromuscular electrical stimulations. A Russian physiologist [18] reported that using a frequency of 2.500 Hz; increased the muscle strength of the healthy subjects by 30-40 % in 20 sessions. Each session consists of 10 contractions in 10 seconds, each with 50 seconds' rest [17] which is considered a highly recommended protocol (10/50/10); where the stimulation to trigger muscle contraction is applied for 10 seconds, followed by off time for 50 seconds, and this cycle is continuously repeated 10 times. [19-21]

Expert modes are an option that can be selected after setting the electrical stimulator parameters, for example: carrier frequency, duty cycle, and burst duration. This option allows the therapist to modulate the stimulus in three diverse ways.

ON2mode; consists of two intervals the stimulus will be applied as; preset on the device, following by 2 second off and then and ON2 stimulus that has a frequency of 50 Hz and 100% amplitude.

Rest mode: consist of two intervals the stimulus will be applied as; preset on the device, then follow by a continuous Rest stimulus that has a frequency of 24 Hz and 83% amplitude.

Although, there has been a many studied that investigate the impact of several parameters on the quadriceps muscle's EIT, but no research demonstrates the relationship between expert modes and the increase electrically induced isometric quadriceps torque during the application of burst modulated alternating current at a specific peak current intensity. Since NMES is widely used to strengthen the quadriceps muscle, the impact of expert RC electrical stimulator modes on electrically induced quadriceps forces may offer further data to assist physicians in choosing the best stimulation parameters. Accordingly, this study's aim is to determine the electrically induced torque responses of the quadriceps to three expert types of burst-modulated alternating current at a particular peak current intensity. The results of this study could aid practitioners in using various parameters to improve muscle training at current amplitudes. With understanding of how different modes affect the intensity of muscular training, the physician could be able to provide the most effective NMES strength-training program.

## **2. Methods**

### **2.1 Elaboration protocol**

The protocol for the study was created in accordance with the SPIRIT guidelines [22] and is also reported in accordance with the CONSORT statement [23]. Figure 1 illustrates the schedule of assessments at various points in time.

### **2.2 Study design**

A single blinded randomize controlled trial.

|                                                                                | Study period   |            |                      |  |  |  |  |  |   |                           |                           |
|--------------------------------------------------------------------------------|----------------|------------|----------------------|--|--|--|--|--|---|---------------------------|---------------------------|
|                                                                                | Enrollmen
t | Allocation | Intervention         |  |  |  |  |  |   | Post
Interventio
n  | Follow -up                |
| TIMEPOINT                                                                      | -t1            | 0          | Three weeks, 2x/week |  |  |  |  |  |   | 3 rd week (t1) | 6 th week (t2) |
| ENROLMENT:

Eligibility screen

Informed consent

Allocation |                |            |                      |  |  |  |  |  |   |                           |                           |
|                                                                                | x              |            |                      |  |  |  |  |  |   |                           |                           |
|                                                                                | x              |            |                      |  |  |  |  |  |   |                           |                           |
|                                                                                |                | x          |                      |  |  |  |  |  |   |                           |                           |
| INTERVENTION:

OFF-MOOD (RC)

ON-MOOD

ON2-MOOD              |                |            |                      |  |  |  |  |  |   |                           |                           |
|                                                                                |                |            | ←                    |  |  |  |  |  | → |                           |                           |
|                                                                                |                |            | ←                    |  |  |  |  |  | → |                           |                           |
|                                                                                |                |            | ←                    |  |  |  |  |  | → |                           |                           |
| ASSESSMENT:

List base line variable

List outcome variable        |                |            |                      |  |  |  |  |  |   |                           |                           |
|                                                                                |                | x          |                      |  |  |  |  |  |   |                           |                           |
|                                                                                |                |            |                      |  |  |  |  |  | x | x                         |                           |

FIGURE 1. SPIRT SCHEDULE OF ENROLLMENT, INTERVENTION, AND ASSESSMENT. THIS LIST INCLUDES THREE TIME POINTS. WHICH ARE BEFORE THE START OF INTERVENTION T0, AT THE END OF RC TRAINING T1, AND AT FOLLOW UP T2.

### 2.3 Study setting and eligibility criteria

This research will be conducted in the University of Sharjah physiotherapy laboratory, UAE. Healthy volunteer subjects of both sexes will participate in this study. The participants will be chosen from among university students via an outside posted volunteer sign-up sheet and a mass e-mail sent to all students. Before participation, all participants will sign a written consent

form that includes agreement to participation and publication of the results, as approved by the Research Ethics Committee of the University of Sharjah. The participant will be informed that the study's purpose is to measure the output torque of the knee extensor caused by different modes of RC electrical stimulation. Interested participants will then undergo an eligibility assessment by a physical therapist before the recruitment. A general medical questionnaire will be filled out by the participant as a baseline assessment that will include age, gender, BMI, and history. The collection of data will take place in the physiotherapy department lab at the University of Sharjah.

The subjects will be selected according to the following criteria: Their age ranged from 18 to 25 years, the BMI (body mass index) is within the normal range (20-25), do not have any medical conditions that have necessitated medical attention in the last two years. The subjects will be excluded from this study if they have any of the following criteria: quadriceps muscle injury spinal or lower limb fractures, lower limb deformities, abnormalities in cognition that may affect muscle and limb function, tumors or radicular symptoms, recent muscular lesions, knee injuries, sensory changes, and neuromuscular diseases; Previous surgeries that may affect the lower limb muscle performance. Any contraindication for the current Russian application. (Table1). (Table1)

TABLE 1: INCLUSION AND EXCLUSION CRITERIA FOR RC STUDY

| Inclusion criteria | Exclusion criteria |
|--------------------|--------------------|
|--------------------|--------------------|

- 
- |                                                                                                                                                                                                                  |                                                                                                                                                                                                                                                                                                                                                                                                                                                                    |
|------------------------------------------------------------------------------------------------------------------------------------------------------------------------------------------------------------------|--------------------------------------------------------------------------------------------------------------------------------------------------------------------------------------------------------------------------------------------------------------------------------------------------------------------------------------------------------------------------------------------------------------------------------------------------------------------|
| 
 
• Age from 18 to 25 years
 
• BMI range 20-25
 
• Do not have any health-related condition that required medical attention in the past two years
 
 | 
 
• Quadriceps muscle injury
 
• Spinal or lower limb fractures
 
• Lower limb deformities
 
• Associated cognition abnormalities which may affect muscle and limb function.
 
• Tumors or radicular symptoms
 
• Recent muscular lesion, knee injury, sensory changes, and neuromuscular disease
 
• Previous surgery that may affect the lower limb muscle performance
 
 |
|------------------------------------------------------------------------------------------------------------------------------------------------------------------------------------------------------------------|--------------------------------------------------------------------------------------------------------------------------------------------------------------------------------------------------------------------------------------------------------------------------------------------------------------------------------------------------------------------------------------------------------------------------------------------------------------------|
- 

158    Contraindications to electrical muscular stimulation listed according to guidelines “Electrophysical Agents-  
 159    Contraindications and Precautions: An Evidence –Based Approach to Clinical Decision Making in Physical  
 160    Therapy” by Houghton, Nussbaum, and Hoens. (Table 2) [24]

161    **TABLE 2. SUMMARY OF ELECTRICAL STIMULATION RECOMMENDATIONS**

|                                                                                                                                                                                                                                                                                                                                                                                                                                                                                                                                                                                                                                                                                                                                                                                                                                                                                                                                                                                                                                                                                                                                                                                                               |
|---------------------------------------------------------------------------------------------------------------------------------------------------------------------------------------------------------------------------------------------------------------------------------------------------------------------------------------------------------------------------------------------------------------------------------------------------------------------------------------------------------------------------------------------------------------------------------------------------------------------------------------------------------------------------------------------------------------------------------------------------------------------------------------------------------------------------------------------------------------------------------------------------------------------------------------------------------------------------------------------------------------------------------------------------------------------------------------------------------------------------------------------------------------------------------------------------------------|
| 
Electrical stimulation (all forms) should not be applied
 
 
• to areas where it could cause malfunction of electronic devices, including cardiac pacemakers.
 
• to areas where malignancy is known or suspected.
 
• to people who have thrombophlebitis or active deep vein thrombosis.
 
• to individuals with untreated hemorrhagic diseases or to tissue that is actively bleeding.
 
• to infected tissues, tuberculosis, or wounds with underlying osteomyelitis.
 
• to recently radiated tissues
 
• to damaged or at-risk skin areas that would result in uneven conduction of current (excluding open wounds where the specific intent is to use electrical stimulation for tissue healing). TENS should not be applied
 
• to areas that have impaired sensory awareness
 
• NMES should not be used on pregnant women (anywhere), patients with cognitive or communication problems severe enough to prohibit them from providing accurate and timely feedback, and areas with poor circulation and any unstable area due to recent surgery, bone fracture, or osteoporosis
 
 |
|---------------------------------------------------------------------------------------------------------------------------------------------------------------------------------------------------------------------------------------------------------------------------------------------------------------------------------------------------------------------------------------------------------------------------------------------------------------------------------------------------------------------------------------------------------------------------------------------------------------------------------------------------------------------------------------------------------------------------------------------------------------------------------------------------------------------------------------------------------------------------------------------------------------------------------------------------------------------------------------------------------------------------------------------------------------------------------------------------------------------------------------------------------------------------------------------------------------|

**Electrical stimulation (all forms) can be applied with caution**

- to active epiphysis
- persons with skin diseases (e.g., eczema, psoriasis)
- persons with cognition or communication impairments sufficient to prevent them from giving accurate and timely feedback e areas of impaired sensation that prevent accurate and timely feedback
- to areas with impaired circulation, if pain is not exacerbated

## **2.4 Study procedure and outcome measurement**

Before taking part in the study, all eligible volunteers will be given information about it and asked to sign an informed consent form before the stimulation session. Baseline assessment will include demographic information, and the MVIC will be collected prior to stimulation sessions. The evaluation of primary and secondary outcomes will take place at the end of the intervention, three weeks after randomization, and at the six-week follow-up. The flow of participants throughout the investigation is represented in Fig. 2.

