### **Primary outcome measure**

Considering the potential advantages of NMES for enhancing muscle performance and the dearth of research in this area, the main objective of this study will be directed to evaluate the impact of various Russian current expert modes on the maximum electrically induced torque of the quadriceps femoris, and to compare the electrically elicited knee extensor torque at the maximal stimulation tolerance level using 3 different RC experts' modes (off mode, on mode and on2 mode).

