positioned just above the ankle malleoli, while the lateral epicondyle of the knee will be in line with the axis of rotation of the lever arm. The participant's peak knee extension torque will be determined using an MVIC performed at 90° of knee flexion against the isokinetic dynamometer's resistance arm. After being correctly seated in the Biodex device, and prior to the application of stimulation, participants will be asked to perform a minimum of three maximum voluntary isometric contractions (MVIC). The participant is required to hold each contraction for around five seconds and rest for 120 seconds (about two minutes) in between each contraction. The highest peak torque generated during the three maximum-effort trials will be called KEMVIT, where the maximum volitional peak knee extensor muscle torque (Newton meters) will be recorded using a Biodex as a baseline measurement. For instance, if there is an increase in the maximum torque by more than 5% on the third attempt, the participants will be asked to continue the contraction efforts until the increase in maximum peak torque decreases to less than 5%. The peak torque produced during the testing will be used to normalize the RC-elicited knee extensor torque to produce a percent of KEMVIT (%KEMVIT), a verbal encouragement will be given to the participants by the examiner to promote maximal effort during all contractions.

In the same position used to determine the maximum torque, RC stimulation will be administered. Two channels will be used for delivering the electrical stimulus: On the anterior thigh, four circular cutaneous electrodes with a 7.6-cm diameter will be placed. The anode will be positioned distally over the vastus medialis, with the cathode being positioned proximally over the rectus femoris. Prior to beginning testing, participants will be instructed to relax during the electrical stimulation application so that all knee extensor torque production comes directly from the electrical stimulation rather than the quadriceps muscle voluntary contraction. Participants will be monitored and instructed to self-report pain on an 11-point (0–10) numeric pain-rating scale after each

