contraction, with 0 indicating "no pain" and 10 the "worst pain imaginable." Participants will be informed that a pain level of 7/10 is the maximal acceptable pain, If the pain rating reaches 7/10 or if they decide to discontinue testing for any other reason, the trials will be discontinued immediately. Similarly, the participants will be instructed to stop stimulation at a similar level of discomfort. Individuals will be submitted to the following 3 randomized test conditions, and the electrically RC elicited isometric knee extensor torque will be measured in response to each of the modes at the participants' maximum tolerance. RC stimulation session will last for 15 minutes. The Russian current neuromuscular electrical stimulation will be administered using a Chattanooga Forte 200 Combo stimulator (DJO Global, Vista, CA). The Russian currents produce 50 bursts per second at a carrier frequency of 2500 Hz, with each burst lasting 10 milliseconds and followed by a 10-millisecond inter-burst gap, resulting in a 50% duty cycle and a 200-microsecond phase duration as a fixed parameter. which automatically adjust the 3 expert modes:

OFF mode;

ON2mode; consists of two intervals the stimulus will be applied as; preset on the device, following by 2 second off and then and ON2 stimulus that has a frequency of 50 Hz and 100% amplitude.

Rest mode; consist of two intervals the stimulus will be applied as; preset on the device, then follow by a continuous Rest stimulus that has a frequency of 24 Hz and 83% amplitude.

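### The protocol is inconsistent on whether the primary outcome, electrically elicited torque, is measured before training

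*Protocol*

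**What the plan says.** The primary outcome in section 2.4 is electrically elicited torque. The aim is "to compare the electrically elicited knee extensor torque at the maximal stimulation tolerance level using 3 different RC experts' modes". The secondary outcome is discomfort.

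Five places bear on when these are measured:

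- **Abstract, Methods.** Elicited torque "will be measured in response to modes at the participants' maximum tolerance at three points before the start of training", then after three weeks of training and at the six-week follow-up.
- **Section 2.4, opening paragraph.** "Baseline assessment will include demographic information, and the MVIC will be collected prior to stimulation sessions". The following sentence reads "The evaluation of primary and secondary outcomes will take place at the end of the intervention, three weeks after randomization" and adds the six-week follow-up.
- **Section 2.2, Figure 1 caption.** It lists three time points, "WHICH ARE BEFORE THE START OF INTERVENTION T0, AT THE END OF RC TRAINING T1, AND AT FOLLOW UP T2", without saying which variables belong to which.
- **Section 2.9.** The voluntary peak torque (KEMVIT) "will be recorded using a Biodex as a baseline measurement". Later in the section, "the electrically RC elicited isometric knee extensor torque will be measured in response to each of the modes at the participants' maximum tolerance", with no visit named.
- **Section 2.10.** Initial data are gathered before the programme and again at weeks 3 and 6. The variables are not named.

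**The concern.** The abstract gives the primary outcome three measurement times and section 2.4 gives it two. The missing one is the pre-training value. An examiner who works from section 2.4 would have no instruction to record elicited torque or a discomfort rating before training starts, and a measurement missed then cannot be recovered. A statistical analysis plan can choose covariates, but it cannot supply a value that was never taken, so visit content has to be right in the protocol.

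Baseline MVIC does not fill the gap. It is voluntary torque, and section 2.9 uses it as the denominator that turns elicited torque into a percentage of KEMVIT. It is a different quantity from the primary outcome.

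At stake are any estimate of change in elicited torque from before training, and the precision that a baseline value of the same variable would bring to the comparison of modes.

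**Working it through.** **Step 1: the passages side by side.**

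| Place | Elicited torque before training? | At 3 weeks | At 6 weeks |
|---|---|---|---|
| Abstract, Methods | Yes | Yes | Yes |
| Section 2.4 | Not scheduled | Yes | Yes |
| Figure 1 caption | T0 named, variable not named | T1 | T2 |
| Section 2.9 | Test described, no visit named | – | – |
| Section 2.10 | Data collected, variable not named | Data | Data |

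The outcome sentence in section 2.4 could be read as listing two times (end of intervention being the same as three weeks) or three. Either way all of them fall after randomisation and none before training. The Figure 1 grid is not relied on, because its layout may have been damaged in extraction.

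**Step 2: inputs for an illustration of size.** The contradiction itself needs no arithmetic.

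- Difference 1.5 and SD 2.5 (section 2.7): d = 1.5/2.5 = 0.6.
- 66 participants in three groups (abstract): 66/3 = 22 per arm. With 10% dropout (section 2.7), 22 × 0.9 = 19.8, taken as 20.
- Significance level 0.05 (section 2.7). Two-sided is assumed, since the protocol does not say.
- SD 2.5 is assumed to be that of a single measurement. Section 2.7 does not say.
- The correlation r between baseline and follow-up elicited torque is assumed. The protocol gives none.

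**Step 3: the stated sample size.** The usual two-group formula gives 2 × 2.5² × (1.960 + 0.842)² / 1.5² = 43.6, so 44 per arm and 132 in all before dropout. That is not 66. The one-sample or paired formula, 2.5² × (1.960 + 0.842)² / 1.5² = 21.8, gives 22, and 3 × 22 = 66 with no dropout added. The mismatch is a separate matter. It is shown here because it explains why the unadjusted power below is well under 80%.

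**Step 4: power for one pairwise comparison.** Two-sample t-test with 20 per arm. Adjusting for a baseline covariate shrinks the SD by √(1 − r²), so the effective difference is d′ = 0.6/√(1 − r²). The equivalent unadjusted size is 20/(1 − r²).

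| r (assumed) | Residual SD | d′ | Power | Equivalent n per arm |
|---|---|---|---|---|
| 0 (no baseline) | 2.50 | 0.60 | 46% | 20 |
| 0.3 | 2.38 | 0.63 | 49% | 22 |
| 0.5 | 2.17 | 0.69 | 57% | 27 |
| 0.7 | 1.79 | 0.84 | 74% | 39 |
| 0.8 | 1.50 | 1.00 | 87% | 56 |

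**The case against.** The strongest reply is that the measurement is probably intended. The abstract schedules it outright, the Figure 1 caption has a T0, and section 2.10 collects data before the programme. Section 2.9 can be read as a single session in which MVIC is taken and elicited torque is then measured in the same position, which would supply a T0 value. Section 2.4 says what baseline assessment will include, which is not an exhaustive list.

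This stands as far as it goes. A reader might infer from section 2.4 that the trial collects nothing but demographics and MVIC at baseline, and so has no baseline for its primary outcome. The documents do not support that: it follows only if section 2.4 overrides the abstract, and nothing says it does. But the reply does not remove the inconsistency. The abstract is the only place that puts elicited torque before training, and the outcome schedule in section 2.4 omits that visit.

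A second tempting inference is that the comparison of modes would be invalid or uncorrectable without the baseline. That is also not supported. Allocation is randomised and stratified by gender (section 2.5), MVIC and gender remain available for adjustment, and expressing torque as a percentage of KEMVIT already removes some variation between people.

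Third, the power gains are conditional. If SD 2.5 describes a change rather than a single value, the baseline is already built in and the gains in the table do not apply. They also presume a baseline-adjusted model, whereas section 2.10 names descriptive statistics and Pearson correlation.

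**Conclusion.** The inconsistency is real and should be resolved before data collection. Three measurement times for the primary outcome in the abstract cannot stand beside two in section 2.4, and no other passage decides between them.

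The consequence is conditional. If section 2.4 governs, change in elicited torque and in discomfort cannot be estimated and precision is lost, while the randomised contrast remains valid. The size of the loss depends on a correlation that the protocol does not give. It is small at 0.3 (46% to 49% power) and large at 0.8 (46% to 87%), with SD 2.5 read as that of a single measurement and 20 completers per arm.

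Confidence is high in the contradiction. The figures are an illustration of what a baseline value could be worth.

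**What to change.** Reconcile the abstract, the Figure 1 caption and sections 2.4, 2.9 and 2.10:

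1. Amend section 2.4 to state that elicited torque and the 0–10 discomfort rating are measured at t0 as well as at t1 and t2, as the abstract already says for torque. Name the variables collected at T0 in Figure 1 and section 2.10, and name the visits in section 2.9.
2. State the test condition used at t0. If t0 is measured before the allocation is revealed, the condition must be one common to all arms. It cannot be the allocated mode, which is not yet known. Section 2.9 leaves open whether each participant is tested in one mode or in all three, so this has to be settled first.
3. Use the t0 elicited torque as a covariate in the comparison of elicited torque between groups.

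If no pre-training measurement is intended, the abstract must change instead, and the loss described above is accepted.

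The cost is more than a wording change in section 2.4, though still modest. The participant is already seated in the dynamometer for MVIC, so t0 adds a few minutes and one stimulated test. The test condition must be defined, and section 2.10 needs a baseline-adjusted model that it does not now specify.
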